#### Secondary outcomes

Secondary outcomes are collected up to 3 months after the last day of ICU stay (ie, the day of ICU discharge that is not followed by any ICU readmission during the index hospitalisation); they are listed in tables1^7^.

**Table 1 T1:** Clinical outcome measures (hospital stay)

Outcome measure	Measure description	Time frame
Maximum SOFA Score	Maximum sepsis-related organ failure assessment score, including a derived delta SOFA (total maximum SOFA minus admission SOFA) as a descriptor of multiple organ dysfunction.	During ICU stay (average ~7–9 days)
Incidence of delirium	Occurrence of delirium measured by validated delirium scoring instruments.	During ICU stay (average ~7–9 days)
ICU complications	Occurrence of any complication impacting length of stay and mortality. Captured by the question: CPR, tracheostomy, major surgery due to complication or none.	During ICU stay (average ~7–9 days)
Presence and nature of treatment limitations	Documentation of treatment limitations (eg, restrictions on frequency, scope or duration of interventions).	During ICU stay (average ~7–9 days)
ICU mortality (yes/no)	Whether the patient died during the ICU stay.	During ICU stay (average ~7–9 days)
Readmissions to ICU	The frequency at which patients, after being transferred out of the ICU, are readmitted to the ICU.	During hospital stay (expected average ~14–16 days)
Length of hospital stay	Total number of days from hospital admission to hospital discharge.	During hospital stay (expected average ~14–16 days)
Discharge destination (ICU)	Recorded destination on ICU discharge. Options include: hospital unit, other ICU in the hospital, external ICU, skilled nursing facility, rehabilitation unit, palliative care unit, hospice, home or other.	During hospital stay (expected average ~14–16 days)
Discharge destination (hospital)	Recorded destination on hospital discharge. Options include: skilled nursing facility, rehabilitation unit, palliative care unit, hospice, home or other.	During hospital stay (expected average ~14–16 days)
Hospital mortality (yes/no)	Whether the patient died during the overall hospital stay.	During hospital stay (expected average ~14–16 days)
Days of mechanical ventilation	Total number of days the patient received invasive mechanical ventilation.	During ICU/hospital stay
Days of ECMO	Total number of days the patient was supported by ECMO.	During ICU stay
Days of RRT	Total number of days the patient received renal replacement therapy (eg, dialysis).	During ICU/hospital stay
Days of LRT	Total number of days the patient received liver support therapy.	During ICU stay
Days of VADs	Total number of days the patient was supported by ventricular assist devices (eg, LVAD, RVAD, Impella, IABP).	During ICU/hospital stay

Impella: a percutaneous left ventricular assist device.

CPR, cardiopulmonary resuscitation; ECMO, extracorporeal membrane oxygenation; IABP, intra-aortic balloon pump; ICU, intensive care unit; LRT, liver replacement therapy; LVAD, left ventricular assist device; RRT, renal replacement therapy; RVAD, right ventricular assist device; SOFA, Sequential Organ Failure Assessment; VAD, ventricular assist device.

**Table 2 T2:** Process and patient-centred/family-centred outcome measures (hospital stay)

Outcome measure	Measure description	Time frame
Quality of life and health status	Quality-of-life score as measured by the EQ-5D-5L plus a 0–100 VAS rating of overall health status; scores correspond to day 14 before ICU admission, to day 1 of study enrolment and to day of ICU discharge	Up to ICU discharge
Palliative care assessment	Whether a palliative care assessment was performed (yes/no).	During ICU stay (average ~7–9 days)
Specialised palliative care expert consultation	Documentation of whether a specialised palliative care expert was consulted (yes/no), reflecting added multidisciplinary support for patient and family.	Until hospital discharge (expected average ~14–16 days)

* Retrospective assessment of quality of life.

EQ-5D-5L, European Quality of life-5 Dimensions 5-Level; ICU, intensive care unit; VAS, Visual Analogue Scale.

**Table 3 T3:** Patient follow-up outcomes (3-month
follow-up)

Outcome measure	Measure description	Time frame
Level of distress at present time point	Rating on a numeric scale from 0 (no distress) to 10 (extreme distress).	Up to 3 months after ICU discharge
Anxiety and depression	Rating of responses to the four questions of the Patient Health Questionnaire 4, according to a four-point scale, ranging from ‘not at all’ to ‘nearly every day’.	Up to 3 months after ICU discharge
Satisfaction with quality of symptom control in the ICU	Rating of management of pain, breathlessness and anxiety/fear/agitation according to a five-point Likert scale, ranging from ‘excellent’ to ‘poor’.*	Up to 3 months after ICU discharge
Adequacy of explanation of treatment by ICU clinicians	Rating according to a four-point Likert scale, ranging from ‘very well’ to ‘not at all’.*	Up to 3 months after ICU discharge
Effort by ICU clinicians to obtain information about the patient’s treatment goals	Rating according to a four-point Likert scale, ranging from ‘very well’ to ‘not at all’.*	Up to 3 months after ICU discharge
Alignment of intensity and duration of ICU therapy with patient’s wishes	Rating according to a three-point Likert scale (‘too much’,‘just right’,‘too little’).*	Up to 3 months after ICU discharge
Quality of life and health status	Quality of life score as measured by the EQ-5D-5L plus a 0–100 VAS rating of overall health status; scores correspond to day 28† and day 90 after ICU discharge	Up to 3 months after ICU discharge
Facilitators for high-quality palliative care	Open-ended response identifying key factors that promote high-quality palliative care.	Up to 3 months after ICU discharge
Barriers to high-quality palliative care	Open-ended response identifying factors that hinder high-quality palliative care.	Up to 3 months after ICU discharge

* For all Likert-scale items, responses were offered on the stated scale along with an additional ‘no answer/can’t say’ option.

† Retrospective assessment of quality of life.

EQ-5D-5L, European Quality of life-5 Dimensions 5-Level; ICU, intensive care unit; VAS, Visual Analogue Scale.

**Table 4 T4:** Relative follow-up outcomes (3-month
follow-up)

Outcome measure	Measure description	Time frame
Satisfaction with quality of symptom control of loved one in the ICU	Rating of management of pain, breathlessness and anxiety/fear/agitation according to a five-point Likert scale, ranging from ‘excellent’ to ‘poor’.*	Up to 3 months after ICU discharge
Relative’s feeling of being included in ICU decision-making	Rating according to a five-point Likert scale, ranging from ‘very excluded’ to ‘very included’.*	Up to 3 months after ICU discharge
Adequacy of support for relative during ICU decision-making	Rating according to a five-point Likert scale, ranging from ‘totally unsupported’ to ‘very supported’.*	Up to 3 months after ICU discharge
Relative’s perceived control over patient’s ICU care	Rating according to a five-point Likert scale, ranging from ‘really out of control’ to ‘good control’.*	Up to 3 months after ICU discharge
Adequacy of time for the addressing of concerns and questions associated with decisions made during ICU stay	Rating according to a five-point Likert scale, ranging from ‘definitely inadequate’ to ‘substantial amount’.*	Up to 3 months after ICU discharge
Adequacy of explanation of loved one’s treatment by ICU clinicians	Rating according to a four-point Likert scale, ranging from ‘very well’ to ‘not at all’.*	Up to 3 months after ICU discharge
Effort by ICU clinicians to obtain information about the patient’s treatment goals	Rating according to a four-point Likert scale, ranging from ‘very well’ to ‘not at all’.*	Up to 3 months after ICU discharge
Perception of unnecessary prolongation of loved one’s life in the ICU	Rating according to a five-point Likert scale regarding the degree to which life was prolonged unnecessarily.*	Up to 3 months after ICU discharge
Evaluation of loved one’s comfort in their final hours before death in the ICU	Rating according to a five-point Likert scale, ranging from ‘very uncomfortable’ to ‘totally comfortable’.*	Up to 3 months after ICU discharge
Perception of healthcare team support for the relative during the loved one’s final hours before ICU death	Rating according to a five-point Likert scale, ranging from ‘very abandoned’ to ‘very supported’.*	Up to 3 months after ICU discharge
Facilitators for high-quality palliative care	Open-ended response on factors promoting high-quality palliative care, as perceived by relatives.	Up to 3 months after ICU discharge
Barriers for high-quality palliative care	Open-ended response on factors hindering high-quality palliative care, as perceived by relatives.	Up to 3 months after ICU discharge

* For all Likert-scale items, responses were offered on the stated scale along with an additional ‘no answer/can’t say’ option.

ICU, intensive care unit.

**Table 5 T5:** Resource utilisation outcomes

Outcome measure	Measure description	Time frame
Days of mechanical ventilation	Total number of days the patient received invasive mechanical ventilation. (Note: mechanical ventilation may be provided both in ICU and non-ICU settings.)	During ICU/hospital stay
Days of RRT	Total number of days the patient received renal replacement therapy (eg, dialysis). (Note: RRT may be provided in both ICU and non-ICU settings.)	During ICU/hospital stay
Days of VADs	Total number of days the patient was supported by ventricular assist devices (eg, LVAD, RVAD, Impella, IABP). (Note: VAD support can occur both in and outside the ICU.)	During ICU/hospital stay
Days of ECMO	Total number of days the patient was supported by extracorporeal membrane oxygenation. (ECMO is exclusively provided in the ICU.)	During ICU stay
Days of LRT	Total number of days the patient received liver replacement therapy. (LRT is generally confined to the ICU.)	During ICU stay
Length of hospital stay	Total number of ICU and non-ICU days during index hospitalisation.	During hospital stay (expected average 14–16 days)
Outpatient resource utilisation	Number of outpatient visits the patient after the index hospitalisation, by type of provider.	Up to 3 months after hospital discharge
Rehospitalisations	Number and/or total days of rehospitalisations experienced after the index hospitalisation.	Up to 3 months after hospital discharge
Days in care institutions	Total number of days spent in rehabilitation centres, long-term care facilities or other care institutions after the index hospitalisation.	Up to 3 months after hospital discharge
Outpatient nursing services	Total amount of outpatient nursing care received (eg, number and duration of home nursing visits) after the index hospitalisation.	Up to 3 months after hospital discharge
Specialised outpatient palliative care	Use of specialised outpatient palliative care services (eg, number of visits) after the index hospitalisation.	Up to 3 months after hospital discharge
Provision of informal care by family members	Yes, or no, or unknown; if yes, number of hours per week	Up to 3 months after hospital discharge

Impella: a percutaneous left ventricular assist device.

ECMO, extracorporeal membrane oxygenation; IABP, intra-aortic balloon pump; ICU, intensive care unit; LRT, liver replacement therapy; LVAD, left ventricular assist device; RRT, renal replacement therapy; RVAD, right ventricular assist device; VAD, ventricular assist device.

**Table 6 T6:** Health economics outcomes

Outcome measure	Measure description	Time frame
Costs	Comprehensive costs derived from hospital cost and billing data, including data on medical resource consumption and intervention costs (eg, staff time for palliative care activities combined with salaries per occupational group).	Measured during the index hospitalisation (ICU/hospital stay) and up to 3 months after hospital discharge
Cost-effectiveness, cost–consequence situation	Economic evaluation putting cost data in relation to patient and family outcomes.	Up to 3 months after hospital discharge

ICU, intensive care unit.

**Table 7 T7:** Clinician-related outcome measures*

Outcome measure	Measure description	Time frame
Burnout assessment	BAT-12 Short version, 12 questions	Up to 34 months
Inappropriate therapy	Perception of inappropriate therapy, 5 questions, answer format 5-point Likert scale (ranging from ‘never’ agree to ‘very often’)	Up to 34 months
Moral distress	Moral distress is measured per employee using a (0–10) numeric rating scale	Up to 34 months
End-of-life practice	12 questions regarding the current implementation of end-of-life practice, yes–no answer format	Up to 34 months
Ethical decision-making climate in the ICU	8 items, answer format 5-point Likert scale (ranging from ‘strongly agree’ to ‘strongly disagree’)	Up to 34 months
Existence of standard operating procedures	4 questions about the presence of written ICU protocols, yes–no answer format	Up to 34 months
Use of the ABCDEF bundle	11 questions, yes–no answer format	Up to 34 months
Supporting measures for patient/family	4 relevant questions, yes–no answer format	Up to 34 months
Perception of palliative care and law	4 relevant questions, yes–no–don’t know answer format	Up to 34 months
Barriers to palliative care	A multiple choice question	Up to 34 months
Facilitators for palliative care	A multiple choice question	Up to 34 months
Facilitators and barriers for provision of palliative and end-of-life care through telemedicine consultations in the ICU	Three open-ended questions	Up to 34 months

* Clinician outcome data are collected via an electronic questionnaire repeatedly throughout the observation and intervention periods.

A, assess, prevent and Manage pain—ensuring effective pain management using validated scoring instruments; B, Both Spontaneous Awakening Trials and Spontaneous Breathing Trials—performing daily trials to reduce sedation and evaluate readiness for weaning from mechanical ventilation; BAT, Burnout Assessment Tool; C, choice of analgesia and sedation—optimising the selection and management of sedative and analgesic medications; D, delirium—assess, prevent and manage—routinely monitoring for delirium using validated tools and applying preventive/treatment strategies; E, early mobility and exercise—promoting early physical activity and rehabilitation to minimize ICU-acquired weakness; F, family engagement and empowerment—involving family members in care decision; ICU, intensive care unit.

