#### Inclusion criteria

ICU patients with decisional capacity, who can give informed consent for study participation, and incapacitated patients with an available, legally recognised, substitute decision-maker able to provide informed consent on their behalf.Adults aged 18 years and more.The leading cause of critical illness is not cancer; such patients represent a clinically distinct group with different prognosis, pre-existing PC involvement and oncology-specific care pathways that would likely confound the trial’s effect on ICU LOS and other outcomes.^26 27^ Moreover, the most significant evidence gap in the literature on PC for critically ill patients concerns non-cancer populations,^26^,^28^ providing a strong rationale for the inclusion criterion and the design of the present trial.New admission in the participating ICU, with LOS of >72 hours.Need for specialised PC according to attending physician judgement, based on (a) significant disagreement among ICU team members and/or family members about appropriateness of ICU treatment intensity or (b) consideration of therapy limitations or (c) expected benefit from specialised PC consultation for the patient/family and/or ICU team members.

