#### Participant timeline

The data collection timeline is represented in table 8. The collection of secondary outcomes throughout follow-up is also performed for patients who have died before its completion time point (ie, at 3 months after ICU discharge), as applicable.

**Table 8 T8:** Summary presentation of data collection schedule

	Visit 1 study inclusion	Visit - teleconsultation	Visit 2 ICU discharge*	Visit 3 follow-up 3 months post-ICU discharge	
Control phase (CP) Intervention phase (IP)	CP/IP	IP	CP/IP	CP/IP	
Time (hours; days (d))	Any time after 72 hours	<48 hours after inclusion		28 d after ICU discharge (retrospective)	90 d after ICU discharge
Review of inclusion and exclusion criteria, medical history	x				
Information/declaration of consent by legally recognised, substitute decision-maker	x				
Information/declaration of consent by patient	x				
Primary endpoint (ICU length of stay)	x		x		
Secondary endpoints	x	x	x	x	x
Mortality	x	x	x	x	x

* Defined as the last day of ICU stay (ie, the day of occurrence of ICU discharge that is not followed by any ICU readmission during the index hospitalisation); in case of more than one ICU admission during the index hospitalisation, the data on secondary endpoints are (repeatedly) collected on the corresponding days of ICU discharge; however, only the data collected on the last one of the aforementioned ICU discharge days are included in the secondary endpoints’ analyses.

ICU, intensive care unit.

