#### ICU treatment

Data documented by local research teams for all patients while in ICU include:

Baseline data and critical illness characteristics (date and mode of hospital and ICU admission, ICU admission cause/diagnosis, eligibility criteria, documented pre-existing conditions/medical history, illness severity scores).Symptom burden (psychological, physical, social and spiritual) in the context of specialised PC consultation (intervention period only).HRQoL.ICU clinical course data (complications, organ replacement therapy, highest sequential organ dysfunction assessment score, delirium assessment/duration, treatment limitations).Hospital and ICU discharge data (discharge destination (intermediate care/normal care/death) and date).Patient details (unique identifiers, sociodemographic information, health insurance status).

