#### Medical resource use, cost and reimbursement data

Patient-level cost and billing data will be provided by the administrations of participating hospitals. Variables collected at the patient level will cover real costs of healthcare and reimbursements invoiced (including flat-fee reimbursement codes if applicable), between the start of the index hospitalisation and 3-month follow-up (see online supplemental material 8, figure 2).

Medical resource use data, including relevant admission and discharge dates, and information on informal care and resulting productivity losses are collected or extracted from clinical information systems by study staff (until the end of index hospitalisation) or self-reported by patients and relatives (from index hospitalisation’s end to the 3-month follow-up time point). This information will be combined with unit costs either stemming from publicly accessible, external sources or also provided by the hospital administrations. Centre-level unit costs requested from the hospital administrations will include, among others, average daily costs for an ICU, intermediate care or normal ward stay. Additionally, costs related to mechanical ventilation, renal or liver replacement and extracorporeal life support are collected, as well as different types of overhead expenses and salary levels (eg, ICU nurse, ICU physician, PC specialist).

The costs of the intervention will be estimated considering the cost of telemedicine technology (based on information from centres and/or technology providers), staff time (for training, PC consultations) and staff costs per unit of time, by relevant profession. The required information will be covered by the study data collection or provided anonymously/at the hospital level by the centres.

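### Length of hospital stay counts ward days before the first ICU admission, which neither condition can affect; the phase comparison would be more precise and less exposed to admission route if counted from first ICU admission

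*Protocol article*

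**What the plan says.** Under Secondary outcomes, Table 1 defines length of hospital stay as "Total number of days from hospital admission to hospital discharge". Table 5 lists it again as a resource outcome: "Total number of ICU and non-ICU days during index hospitalisation". The two agree, and both start at hospital admission.

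Costs use the same window. Table 6 has them "Measured during the index hospitalisation (ICU/hospital stay) and up to 3 months after hospital discharge", and the section on medical resource use and cost collects billing data "between the start of the index hospitalisation and 3-month follow-up".

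The training, the checklist and factsheet, and the teleconsultations are all directed at ICU staff and ICU patients (sections on the crossover and intervention phases). Enrolment requires "New admission in the participating ICU, with LOS of >72 hours", and Table 8 puts study inclusion at "Any time after 72 hours". The ICU treatment section lists among the recorded items "date and mode of hospital and ICU admission, ICU admission cause/diagnosis".

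The Data analysis plan section makes all secondary endpoints exploratory. The article states no landmark, subtraction or adjustment for hospital days before the ICU.

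**The concern.** A patient transferred from a ward has already spent those ward days before any part of the trial can reach them. The days are a baseline characteristic, yet the definition adds them to the outcome. Two consequences follow.

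- **Noise.** The expected effect on total stay equals the expected effect on stay from first ICU admission, because the pre-ICU part cannot respond. Unless pre-ICU days are sufficiently negatively correlated with later days, including them widens the confidence interval and adds no signal.
- **Admission route.** If the share of ward transfers differs between phases, the difference in mean pre-ICU days enters the hospital-stay contrast in full and could be read as an effect on resource use. Enrolment is unblinded and rests partly on physician judgement, and the training and checklist that may shape that judgement exist only from the crossover onward. A shift is therefore conceivable.

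This differs from ICU days before enrolment, which count in the primary outcome: staff training and tools can act on those days, but nothing in the trial can act on pre-ICU ward days.

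**Working it through.** **1. The plan's own figure.** The article gives no power or precision for hospital stay or costs. Its figure of about 85% is for ICU stay (effect −2 days, SD 9, ICC 0.01, 23 ICUs × 87 = 2001 patients, 35 months). A Hussey–Hughes calculation with 87/34 = 2.56 patients per ICU-month, one excluded crossover month and an assumed schedule of one ICU crossing per month gives SE 0.680 and power 83.7%. The stated figure is thus approximately reproduced. Other evenly spaced schedules give 76% to 93%. None of this depends on pre-ICU days, because the primary outcome counts ICU days only.

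**2. Room for pre-ICU days.** Table 1 expects about 14–16 hospital days and 7–9 ICU days. Non-ICU days are therefore between 14 − 9 = 5 and 16 − 7 = 9. The article does not say how many fall before the ICU.

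**3. Variance, under stated assumptions.** From the documents: ICU stay with mean 9 and SD 9 (variance 81), and total stay with mean 15 (mid-range). Assumed: a fraction p of patients comes from a ward after an exponentially distributed stay with mean m, the others have zero pre-ICU days, post-ICU stay has a coefficient of variation of 1.3 and a mean that brings the total to 15, and the components are independent.

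Pre-ICU variance = 2pm² − (pm)². Post-ICU variance = [1.3 × (15 − 9 − pm)]².

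| | p = 25%, m = 5 | p = 35%, m = 6 |
|---|---|---|
| Pre-ICU mean | 1.25 | 2.10 |
| Pre-ICU variance (SD) | 12.50 − 1.56 = 10.94 (3.3) | 25.20 − 4.41 = 20.79 (4.6) |
| Post-ICU mean; variance | 4.75; 38.13 | 3.90; 25.70 |
| Variance from ICU admission | 81 + 38.13 = 119.13 | 81 + 25.70 = 106.70 |
| Variance of total stay | 130.07 | 127.49 |
| Variance removed by the later start | 10.94/130.07 = 8.4% | 20.79/127.49 = 16.3% |
| SE reduction | 1 − √(119.13/130.07) = 4.3% | 1 − √(106.70/127.49) = 8.5% |
| Equivalent gain in patients | 130.07/119.13 = 1.09, so 9% | 127.49/106.70 = 1.19, so 19% |

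**4. Sensitivity to independence.** With correlation ρ between pre-ICU and later days, total variance exceeds the later variance only if ρ > −SD(pre)/(2 × SD(later)). That is −3.31/(2 × 10.91) = −0.15 in the first scenario and −4.56/(2 × 10.33) = −0.22 in the second. Below those values the noise penalty disappears; a positive correlation makes it larger.

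**5. Admission-route shift.** Shift in mean stay = difference in ward-transfer share × mean pre-ICU days. For an assumed difference of 5 to 10 points and a mean of 5 to 6 days, this is 0.05 × 5 = 0.25 to 0.10 × 6 = 0.60 days, with no treatment effect present. The article contains nothing showing that such a difference will occur.

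**The case against.** Admission to discharge is a common definition of hospital stay, Tables 1 and 5 agree, and the window matches the index hospitalisation used for the primary outcome and costs. Nothing is contradicted, the endpoint is exploratory, and no power is claimed for it. The SAP and the health economic analysis plan, neither of which is shown, may adjust for pre-ICU days, and the data needed are collected. This holds, and it limits the weight of the point. It does not alter that the stay itself is defined in the article with these days included.

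Some stronger readings are not supported:

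- **That the hospital-stay contrast is biased.** Eligibility criteria are identical in both phases, and a change in admission route is only possible. If it occurred, ICU and post-ICU stay could change with it, and a later start would not remove that part.
- **That the loss of precision is large.** Assuming 50% ward transfers with a mean of 7 days gives a variance cut of about 29%, but leaves only 15 − 9 − 3.5 = 2.5 post-ICU days, a split that nothing in the article supports.
- **That whole-episode costs are wrong.** Billing and flat-fee totals cover the hospitalisation, and an institutional perspective is planned, so the whole episode is a legitimate unit there.
- **That all resource items are affected.** ECMO is described as exclusive to the ICU and liver support as generally confined to it. For ventilation, renal replacement and ventricular assist days the point is marginal.

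**Conclusion.** The point holds as a minor improvement to an exploratory outcome. As defined, length of hospital stay includes days that neither condition can change. They add variance and allow any phase difference in admission route into the contrast undiluted.

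Under assumed pre-ICU SDs of about 3–5 days and independence, counting from first ICU admission would cut the variance of hospital stay by about 8–16% and the standard error by about 4–9%. The true size is unknown because the article does not give the split of non-ICU days, and a moderately negative correlation would remove the gain. The case-mix shift is a risk. A reader might infer that the trial's main result or its stated power is in doubt; it is not, because the primary outcome counts ICU days only.

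**What to change.** For the phase comparison, define length of hospital stay in Tables 1 and 5 as days from the first ICU admission of the index hospitalisation to hospital discharge. Tying it to the first ICU admission, not the qualifying one, keeps it consistent with the primary outcome, which counts all ICU days of that hospitalisation. Keep total admission-to-discharge stay as a descriptive figure.

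For index-stay costs, keep the whole-episode window where billing totals or the institutional perspective require it, and include days in hospital before the first ICU admission as a baseline covariate.

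The cost is small: wording in the outcome tables, the SAP and the health economic analysis plan, plus one derived variable from dates already recorded. The compared figure will be less directly comparable with conventional reports, which the descriptive total covers. The change is best made before database lock.
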